### Statistical analyses

2.12

Survey data will be entered into a secure electronic database Castor EDC (Castor Electronic Data Capture, Ciwit Bv, Amsterdam, the Netherlands). Coded data analyses will be performed using SPSS (Release 25, Armonk, NY). Categorical data will be analyzed with the chi-squared test or Fisher's exact test. Differences in 2 and several continuous variables will be assessed by the independent *t* test and one way-ANOVA test, respectively. The normality and homogeneity of variances will be verified, respectively, by Shapiro-Wilk and Levene values >0.05. In case the assumptions for parametric tests are violated, the equivalent Mann–Whitney test and Kruskal-Wallis test will be applied for comparing 2 and several continuous variables, respectively. A multivariate logistic regression model will be used to identify risk factors associated with anti-HBc total positivity. Risk factors that are found to be significantly associated (*P* < .05) with anti-HBc total positivity in univariate analysis will be included as covariates in the logistic regression model. Since all included samples will be linked to questionnaires, corrections for over or undersampling of certain groups will be performed. In order to do this poststratification, weights for age and gender will be created. This will be done for the 2 variables separately, and for their interaction. Chi-squared tests will then be performed again, this time including the poststratification weights. The same will be done for logistic regression. The level of statistical significance is set at *P* < .05.

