## Introduction

1

Hepatitis B virus (HBV) infection is an important public health problem. In the year 2017, approximately 257 million people are chronically infected worldwide and at risk of developing serious sequelae, such as cirrhosis and hepatocellular carcinoma.^[1,2]^

According to the WHO, Turkey is one of the countries with intermediate endemicity for hepatitis B. The hepatitis B surface antigen (HBsAg) prevalence thereby changes from 2% to 3% in the Western part of the country to 7% to 8% in Eastern part.^[3]^ In intermediate endemic countries, such as Turkey, horizontal HBV transmission by nonsexual close contact besides perinatal, sexual, and parenteral transmission is the main route of infection.^[4–7]^ Risk factors associated with horizontal transmission in childhood are poor socioeconomic conditions, the presence of a HBsAg-positive family member and the habit of sharing various personal and household articles within the home (e.g., contaminated toothbrush, contaminated towels).^[5,8,9]^

In contrast, the HBsAg prevalence is low (<1%) in the general population of Belgium and many other Western European countries.^[10,11]^ Sexual transmission of HBV in persons with high-risk sexual behavior (e.g., men who sex with men, heterosexual persons with multiple sex partners) remains a common source of HBV transmission in these low endemic countries.^[2]^

Starting in 1961, political, economic, and social developments led Turkish people to migrate to Europe, Australia, Arab countries, and former Soviet Union countries.^[12]^ According to Turkish government statistics, 5.5 million Turkish citizens live abroad, of whom around 4.6 million live in Western European countries.^[13]^ Turkish citizens are therefore one of the largest migrant groups in Europe. Moreover, a recent study by Ahmad et al^[14]^ indicated that the Turkish population was ranked 3rd as migrant group with the highest absolute number of chronic HBV cases in Europe. However, their estimates of HBsAg prevalence were based on prevalence studies conducted in Turkey. Another study conducted by a Dutch group showed that the Turkish population in the Netherlands had a low level of awareness and knowledge regarding HBV infection which could subsequently impinge the attitude toward HBV screening.^[15]^

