**Table 2 T2:**
[figure not shown]
Barriers for hepatitis B virus screening identified during focus group discussions and actions taken in current study.

As the Islamic mosques mainly consist of male members/visitors, we will also search for female Turkish organizations in the Middle Limburg area. From September 2017 until August 2019, with the support of key figures within these organizations, we will organize educational meetings with the possibility for immediate HBV screening afterwards. The educational and screening sessions will be scheduled after the regular meetings of each organization.

The key figures within these organizations will distribute invitations for the sessions using information flyers, posters, and name cards with a link to the hepatitis B video. The flyers, posters, and video contain information about risk factors for horizontal transmission (sharing personal and household articles, such as toothbrushes) and vertical transmission in addition to general information such as HBV vaccination, consequences of unrecognized HBV, and the possibility of antiviral treatment. Turkish persons who are unable to attend a session will be invited to visit additional educational meetings and screening sessions in Ziekenhuis Oost-Limburg (ZOL) or can make an appointment with [name] at the Hepatology Outpatient Department (OPD) of ZOL. In addition to the abovementioned methods, Turkish people can also contact the first author for home visits with the possibility to sign an informed consent and be screened for HBV. Figure 1 shows the flowchart of the study design.

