### Measures

2.9

Questionnaire: we searched PubMed to identify articles on risk factors for HBV infection in the Turkish community using the following terms and keywords alone and/or in appropriate combinations: hepatitis B, Turkey, Turkish, Turks, risk factor. No publication date or language restrictions were set. In addition, reference lists of all identified articles were checked to identify additional material, including (grey) literature. The final questionnaire includes the following risk factors: blood transfusion (no, yes before 1974 in Turkey, yes before 1974 in Belgium, other), dental treatment (yes in Turkey, other), (if female) gynecological examination (no, yes in Turkey, yes in Belgium, other), (if male) circumcision (no/yes), (if male) circumcision carried out by a doctor (no, yes, unknown), (if male) way of circumcision (alone, collective, unknown), surgery (no, yes in Turkey, yes in Belgium, other), treatment with needles (no, yes in Turkey, yes in Belgium, other), HBV-infected mother (no/yes), HBV-infected father (no/yes), HBV-infected brother (no/yes), HBV-infected sister (no/yes), HBV-infected partner (no/yes), other infected family member (no/yes), sharing toothbrushes with other household members (no, yes once, yes on regular basis), sharing nail clippers with other household members (no/yes), sharing razors with other household members (no/yes), sharing used towels with other household members (no/yes), eating from the same plate as other household members (no/yes), tattoo/piercing/earlobe perforation (no, yes in Turkey, yes in Belgium, other), treatment with Fish spa (no, yes in Turkey, yes in another country than Turkey). Furthermore, the questionnaire will collect data on HBV vaccination (vaccinated no/yes/unknown), (if yes) number of vaccinations, (if no) reasons of not being vaccinated) and previous HBV test results. Data regarding sociodemographics (age, gender, educational status of mother, educational status of father), first language (Dutch/Turkish), migration history (country of birth, (if born in Turkey) year of migration to Belgium, mother's country of birth, father's country of birth, (if mother born in Turkey) region of birth from mother, (if father born in Turkey) region of birth from father) will be collected to characterize the study population. Regarding region of birth, Turkey will be divided in the 7 geographical regions: Marmara, Aegean, Mediterranean, Central Anatolia, Black Sea, Eastern Anatolia, and Southeastern Anatolia (Fig. 2).^[3]^ The questionnaire will not cover questions regarding intravenous drug use or sexual behavior as these questions could lead to a significant lower participation rate and the answers to these questions are not reliable in this Turkish population with a majority being Muslim.

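### The planned tests treat participants as independent, so results for exposures shared within households or families may look more certain than they are

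*Protocol article*

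**What the plan says.** Section 2.12 (Statistical analyses) lists its methods in some detail. "Categorical data will be analyzed with the chi-squared test" or Fisher's exact test; continuous variables get t tests, ANOVA or their rank-based equivalents. For the risk factors, "A multivariate logistic regression model will be used to identify risk factors associated with anti-HBc total positivity", and factors enter that model if their univariate P value is below .05. To correct for over- or under-sampling, "weights for age and gender will be created", after which the chi-squared tests and the regression are repeated with the weights. No clustering, design effect, robust variance or multilevel term is named.

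Other sections bear on whether participants are independent:

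- The Introduction names, as risk factors for horizontal transmission in childhood, poor socioeconomic conditions, "the presence of a HBsAg-positive family member and the habit of sharing various personal and household articles within the home".
- Section 2.4 (Recruitment): "The educational and screening sessions will be scheduled after the regular meetings of each organization". Key figures in those organisations pass on the invitations, and people may ask to be screened at home. No rule limits enrolment to one person per household.
- Section 2.9 (Measures) collects exposures that belong to a household (sharing toothbrushes, nail clippers, razors, towels and plates) or to a family (infected mother, father, siblings or partner, and parents' region of birth).
- Section 3.1 (Strengths and limitations) mentions possible low power for the risk factors but not clustering.

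**The concern.** When people in one household resemble each other in both outcome and exposure, each extra member adds less information than a new independent person. Tests that ignore this give standard errors that are too small, so they reject too often and their intervals are too narrow. The article supplies both ingredients: a reason for infection status to correlate within families, and exposures that family or household members share.

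Risk factors for anti-HBc positivity are a stated aim. The univariate P < .05 filter carries any excess of false positives into the choice of variables for the regression. The weights do not help, because they rebalance age and gender and leave the correlation untouched. If nobody records which participants share a household, the correlation may be hard to measure or correct afterwards.

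**Working it through.** **Inputs from the article.** Planned n = 1000, 95% confidence, margin 3 percentage points and age shares of 54%, 35%, 9% and 1% (Section 2.8); 11,540 adults (Section 2.4); significance level .05, taken as two-sided (Section 2.12); HBsAg prevalence of 3% to 5% in Turkish migrants in neighbouring countries (Discussion), with 4% used for illustration.

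**Inputs assumed.** The article gives neither the number tested per household (m) nor an intraclass correlation (ICC). The ranges below are assumptions.

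**Step 1. The plan's own figure.** For one proportion with finite-population correction, n = N·p·q / [(d/z)²·(N − 1) + p·q], where N = 11,540, d = 0.03 and z = 1.96.

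- p = 0.54: 11,540 × 0.2484 / (0.000234 × 11,539 + 0.2484) = 972 after rounding up.
- p = 0.50: 977.
- p = 0.35, 0.09 and 0.01: 896, 340 and 43.

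The stated 1000 matches the largest of these, rounded up. The calculation contains no design effect, so it takes DEFF = 1.

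**Step 2. Effect of household clustering on a fully shared exposure.** DEFF = 1 + (m − 1)·ICC; effective n = 1000/DEFF; actual error of a nominal 5% test = 2·[1 − Φ(1.96/√DEFF)].

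| m | ICC | DEFF | Effective n | True CI width ÷ reported | Actual error |
|---|---|---|---|---|---|
| 1.5 | 0.05 | 1.025 | 976 | 1.01 | 5.3% |
| 1.5 | 0.1 | 1.05 | 952 | 1.02 | 5.6% |
| 2 | 0.1 | 1.1 | 909 | 1.05 | 6.2% |
| 2 | 0.2 | 1.2 | 833 | 1.10 | 7.4% |
| 3 | 0.2 | 1.4 | 714 | 1.18 | 9.8% |
| 3 | 0.3 | 1.6 | 625 | 1.26 | 12.1% |

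**Step 3. Exposures that are only partly shared.** For a covariate effect, the inflation is roughly 1 + (m − 1)·ICC(outcome)·ICC(exposure).

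- m = 2, outcome ICC 0.2, exposure ICC 0.5: 1 + 1 × 0.2 × 0.5 = 1.10, actual error 6.2%.
- m = 3, outcome ICC 0.3, exposure ICC 0.5: 1 + 2 × 0.3 × 0.5 = 1.30, actual error 8.6%.
- Exposure ICC 0: inflation 1, no effect.
- Exposure ICC −1, as for gender in a mixed-sex couple, with outcome ICC 0.2: 1 − 0.2 = 0.8, so the plain test is conservative.

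**Step 4. HBsAg prevalence.** Half-width = 1.96·√(p·q/1000)·√DEFF. At p = 4% this is ±1.21 points with DEFF 1, ±1.27 with 1.1, ±1.54 with 1.6 and ±1.72 with 2. At p = 5% and DEFF 2 it is 1.35 × 1.414 = ±1.91. All are inside 3 points.

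**Step 5. Clustering by session.** With assumed sessions of 20 to 50 people and ICC 0.005 to 0.02, DEFF is 1.10 to 1.98. This widens a prevalence interval, but it affects an association test only to the extent that the exposure also clusters by session.

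**The case against.** The strongest reply is that the premises are inferred. The article nowhere says that relatives are recruited together. Section 2.4 notes that mosque attendance is mainly male and that women's organisations are approached separately, so sessions may split couples. Only adults are eligible, and 1000 of 11,540 (8.7%) are to be tested, so many households may contribute one person. The family risk factors in the Introduction concern childhood, and spouses tested together may have grown up in different homes. An infected mother is shared by siblings but not by spouses. Infected-relative covariates may absorb part of the correlation in the regression. The article is also condensed: results are posted to participants (Section 2.7), so addresses must be held, and a household link may exist even though no listed questionnaire item provides one.

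Much of this stands, and it rules out four stronger readings that a reader might infer:

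- That families are known to be recruited together. The documents make it likely that some relatives are tested, and no more.
- That every P value is too small. Step 3 shows no effect or a conservative one for exposures that vary within households.
- That household exposures are the main risk-factor question. Section 2.9 also lists transfusion, surgery, needles and other items, and Section 2.11 ranks none of them.
- That the primary outcome is compromised. Section 2.12 specifies no prevalence interval, and Step 4 shows ample precision.

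The reply does not remove the core. Separate male and female sessions do not prevent members of one household from taking part through different routes, and siblings or parents and adult children share family exposures. Section 2.12 does state a method, so this is not merely detail left to another document.

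**Conclusion.** The concern holds in a limited form. The stated tests ignore correlation within households and families, and the weights do not repair this. Results for shared articles, infected relatives and parents' region of birth, and any prevalence interval, may be too optimistic.

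The size cannot be derived from the article. With 2 to 3 people tested per household and ICC 0.1 to 0.3, reported intervals for fully shared quantities would be about 5% to 21% too narrow (1 − 1/1.05 to 1 − 1/1.26), and a nominal 5% test would run at about 6% to 12%. Partly shared exposures are affected less. If few relatives are tested, the error is about 5.3% to 5.6%, which hardly matters. An error rate near 17% would need a design effect of 2, above the household range assumed here.

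This is a worthwhile, inexpensive improvement to the risk-factor analysis. It does not threaten the prevalence estimate's stated margin.

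**What to change.** Record a coded household number and a session or organisation number for each participant, at consent or from the addresses already held. In Section 2.12, replace the independent-data variance by household-cluster-robust variance for the weighted chi-squared tests, the logistic regression and the prevalence interval. GEE logistic regression or the SPSS complex-samples procedures would do this within the software already planned. Add a sensitivity analysis that clusters by session or organisation, since household clustering alone does not cover that level. Report the number of participants per household, so that readers can see how much clustering there was.

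The cost is two coded fields, a change of procedure and somewhat wider intervals. If clustering proves negligible, the results will barely change.

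### The anti-HBc risk-factor model admits covariates only on univariate P < .05 and forces none in, so its associations can remain confounded by age, gender, migrant generation or region of origin

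*Protocol article*

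**What the plan says.** Section 2.12 (Statistical analyses) names the model: "A multivariate logistic regression model will be used to identify risk factors associated with anti-HBc total positivity". Its only entry rule is that risk factors with univariate P < .05 "with anti-HBc total positivity in univariate analysis will be included as covariates in the logistic regression model". No covariate is named as included regardless of its P value.

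In that section age and gender appear by name only in the weighting: "In order to do this poststratification, weights for age and gender will be created". The stated purpose is that "corrections for over or undersampling of certain groups will be performed". The chi-squared tests and the logistic regression are then repeated with the weights.

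Section 2.9 (Measures) lists the risk factors, from blood transfusion to fish spa. Age, gender, parental education, country of birth, year of migration and parental region of birth come afterwards, as data that "will be collected to characterize the study population". Some listed risk factors are asked of one sex only: "if female) gynecological examination (no, yes in Turkey, yes in Belgium, other), (if male) circumcision (no/yes".

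The Introduction says that the HBsAg "prevalence thereby changes from 2% to 3% in the Western part of the country to 7% to 8% in Eastern part", and that universal vaccination began only after 1999 in Belgium and 1998 in Turkey.

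**The concern.** By the protocol's own account, infection varies with region of origin and with vaccination era, and era follows age. Several exposures carry place or era in their answer options: transfusion before 1974, and surgery, needle treatment, dental treatment or piercing in Turkey. These are plausible stand-ins for being older or born in Turkey. A model without age, generation and region can credit such an exposure with an association that belongs to birthplace or birth cohort.

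A univariate screen also works in the other direction. A real factor that is commoner in a low-prevalence group looks weaker before adjustment and may never enter. The factors that do pass tend to have overstated estimates.

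What is at stake is the risk-factor aim. The Abstract and Discussion mean to use it to identify subgroups with higher prevalence and to help stop further spread.

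**Working it through.** **Inputs.** From the protocol: planned n = 1000, significance level .05 (taken as two-sided), and age shares 54/35/9/1%. It gives no anti-HBc prevalence, exposure rate or generation split, so those below are assumptions. No figure in the plan is in dispute. The n of 1000 is close to a ±3% precision calculation: 1.96² × 0.25 / 0.03² = 1067, and with finite-population correction for 11,540 adults 1067 / (1 + 1066/11,540) = 977.

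**1. Generation omitted, true odds ratio 1.** Half the sample is first generation. Within each generation exposure and infection are independent. Cells are proportions of the whole sample; OR = (a/b)/(c/d), with a, b = exposed positive, negative and c, d = unexposed positive, negative.

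| anti-HBc, 1st vs 2nd | exposure, 1st vs 2nd | a | b | c | d | OR |
|---|---|---|---|---|---|---|
| 35% vs 10% | 60% vs 10% | 0.110 | 0.240 | 0.115 | 0.535 | 2.13 |
| 30% vs 10% | 50% vs 20% | 0.085 | 0.265 | 0.115 | 0.535 | 1.49 |
| 30% vs 10% | 40% vs 20% | 0.070 | 0.230 | 0.130 | 0.570 | 1.33 |

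First row: a = 0.5×0.60×0.35 + 0.5×0.10×0.10 = 0.110.

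**2. Do the weights help?** Take three age groups (18–39, 40–59, 60+), an assumed sampled mix of 40/42/18%, population shares 54/99, 35/99 and 10/99 as the weighting target, exposure 20/45/60%, and no effect within age group. There were 1000 simulated studies of n = 1000 per row. The last four columns give the share of studies in which the exposure passes the screen and is also significant in the final model.

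| anti-HBc by age | large-sample OR, unweighted / weighted | no age | no age, weighted | age screened | age forced in |
|---|---|---|---|---|---|
| 8/22/35% | 1.51 / 1.55 | 70.9% | 66.3% | 2.6% | 2.6% |
| 8/15/20% | 1.29 / 1.31 | 26.8% | 23.5% | 2.4% | 2.4% |
| 10/13/16% | 1.14 / 1.14 | 11.6% | 9.1% | 5.4% | 3.0% |

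Weighting changes the population described but does not condition on age, so the odds ratio hardly moves. Age passed its own screen in 100%, 97.9% and 46.3% of studies.

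The screen also inflates what it keeps. Among studies in which the exposure passed, the mean unadjusted OR was 1.64, 1.64 and 1.56, against large-sample values of 1.51, 1.29 and 1.14. Even with age forced in after the screen it was 1.09, 1.26 and 1.37, against a truth of 1.

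**3. If demographics are screened, which would enter?** Approximate power = Φ{(|p₁−p₂| − 1.96·SE₀)/SE₁}, with SE₀ pooled and SE₁ unpooled.

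| anti-HBc contrast | gender, 500/500 | region, 800/200 |
|---|---|---|
| 15% vs 18% | 25% | 19% |
| 15% vs 20% | 55% | 41% |
| 12% vs 20% | 93% | 81% |

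Gender, first row: SE₀ = √(2×0.165×0.835/500) = 0.02348, SE₁ = √((0.1275+0.1476)/500) = 0.02346, and Φ((0.03−0.0460)/0.02346) = 0.25.

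For a confounder this weak, with an even split and a strong 60% vs 10% exposure contrast, a null exposure shows (0.0615/0.2885)/(0.1035/0.5465) = 1.13 at 18% vs 15%, and (0.0675/0.2825)/(0.1075/0.5425) = 1.21 at 20% vs 15%.

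**4. Masking.** Assume 54.5% younger and 45.5% older participants, anti-HBc 8% and 22% in the unexposed, exposure 50% and 25%, and a true OR of 1.7. The crude OR is (0.0720/0.3143)/(0.0969/0.5169) = 1.22. The exposure passed the univariate screen in 21.7% of 1000 simulated studies. With age in the model and no screen it was significant in 83.2%.

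**The case against.** The strongest reply is that section 2.12 bars nothing. It does not define risk factors, and it provides t tests, ANOVA and rank tests for continuous variables, of which the exposure list has hardly any, whereas age and year of migration are continuous. The Discussion wants to know whether second-generation migrants are at risk and says that demographic data allow subanalyses. If generation is screened, the contrasts in step 1 give z = 0.25/√((0.2275+0.09)/500) = 9.9 and 0.20/√((0.21+0.09)/500) = 8.2. It would enter almost surely and the odds ratio would return to about 1.

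That stands as a limit. A reader might infer that the odds ratios must stay confounded; the documents do not support this, because a confounder as strong as those in step 1 would be caught if tested. It does not rescue the rule. Nothing says that the demographic variables are tested, section 2.9 sets them apart from the risk factors, and weaker effects are missed often.

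A reader might also infer that male-only and female-only items in one model would lose half the sample, or all of it. That depends on how inapplicable answers are coded and on which items are selected. The article does not state the coding, and such detail is commonly left to the full protocol or analysis plan.

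Finally, the article speaks of association, not of causal or independent effects, and places this analysis among secondary and exploratory outcomes. It concedes possible low power, though it does not mention confounding. This bears on severity.

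**Conclusion.** The concern holds as a possibility that the plan leaves open, not as a certainty. On the plainer reading, with demographics outside the candidate list, associations can be confounded by all four variables: a null exposure shows an odds ratio of about 1.3 to 2.1 if generation is omitted, under the assumed rates. If demographics are candidates, what remains is confounding by weaker gender or region effects, roughly 1.1 to 1.2 in the cases worked. On either reading the screen can drop masked factors and inflate the ones it keeps, and the weights correct neither problem.

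Every magnitude rests on assumed prevalences, exposure rates and group splits. The protocol's regional figures are for HBsAg, not anti-HBc. The primary outcome, HBsAg prevalence, is unaffected, so this is a should-fix for a secondary aim.

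**What to change.** Amend section 2.12 as follows:

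- Include age, gender, generation (country of birth) and a coarse parental region of origin in the model whatever their univariate P values.
- Give region a category for parents not born in Turkey. Section 2.9 collects region only for Turkish-born parents and section 2.2 requires only one, so participants with a parent born elsewhere would otherwise have missing values.
- Report each exposure adjusted for these variables, in place of the P < .05 screen.
- Keep the poststratification weights for representativeness only.
- Analyse circumcision items in men and gynecological examination in women.

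All the variables are already collected, so the change is one of wording. It costs some degrees of freedom and wider intervals. Seven regions for each parent would take 6 + 6 = 12 degrees of freedom before any further category, which is why a coarse grouping is better. Generation will be partly collinear with exposures located in Turkey, and estimates for those exposures will be less precise.

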### Sample size

2.8

Sample size calculation was performed with the aid of Epi Info (version 7.2, Centers for Disease Control and Prevention [CDC], Atlanta, GA). Considering the lack of data on the number of first and second-generation Turkish migrants living in Middle Limburg, the number of samples per age was calculated instead so that the results of the sample group agree with that of the Turkish population in Middle Limburg with a confidence interval of 95% and 3% as an acceptable margin of error. The expected frequencies for the different age categories 18 to 39, 40 to 59, 60 to 79, and 80+ are 54%, 35%, 9%, and 1%, respectively (Limburg in cijfers, personal communication). Our analysis would lead to a total of 1000 tested persons.

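### The weighted chi-squared tests and logistic regression have no stated variance method; if the weights enter as case counts, their P values are too small

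*Protocol article*

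**What the plan says.** All points are in the protocol article, section 2.12 (Statistical analyses), unless another section is named.

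- The software is SPSS release 25. No survey module or other survey package is named.
- The basic test is fixed: "Categorical data will be analyzed with the chi-squared test or Fisher's exact test".
- A multivariable logistic regression for anti-HBc positivity follows. Its covariates are those with P below .05 in univariate analysis.
- To correct for groups that are over- or under-represented, "In order to do this poststratification, weights for age and gender will be created". There is to be a weight for each variable alone and one for the two combined.
- The tests are then repeated: "Chi-squared tests will then be performed again, this time including the poststratification weights". For the model: "The same will be done for logistic regression".
- One threshold covers everything: "The level of statistical significance is set at *P* < .05".

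The section does not say whether the weights average 1 or sum to the population, or how the variance of a weighted result is estimated. It mentions no confidence interval for a weighted result. Section 2.4 (Recruitment) puts the adult Turkish population of the region at about 11,540. Section 2.8 (Sample size) plans 1000 tested persons and gives the population age shares.

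**The concern.** A post-stratification weight says how many people in the population a participant stands for. It does not say that this many people were observed. An ordinary Pearson chi-squared test or maximum-likelihood logistic regression, run with such weights as case counts, treats a person with weight 3 as three independent people. The point estimates are the intended weighted ones. The standard errors are not: they leave out the variance that unequal weights add, and if the weights do not average 1 they also assume the wrong sample size.

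At stake is the 5% level of the weighted risk-factor analyses, which serve a secondary outcome (section 2.11). The questionnaire in section 2.9 lists 21 risk-factor items, and univariate significance decides which enter the regression. In a weighted re-run, P values that are too small can therefore also carry items into the model.

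Some imbalance is foreseeable. Section 2.4 notes that mosque visitors are mainly men, and section 2.12 itself plans to correct for uneven sampling. The more the weights are needed, the more they vary, and the worse an uncorrected test performs.

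**Working it through.** **The plan's own figures.** The documents give no design effect, weighted P value or weighted interval, so there is no figure of that kind to reproduce. The one figure borrowed is the planned size: "Our analysis would lead to a total of 1000 tested persons". Section 2.8 aims at agreement with the population "with a confidence interval of 95% and 3% as an acceptable margin of error". The single-proportion formula with finite population correction is n = N·p(1−p) / [(d²/z²)(N−1) + p(1−p)]. With N = 11,540, d = 0.03 and z = 1.96 it gives 972 for p = 0.54 and 977 for p = 0.50, in line with 1000. This confirms the input and does not decide the point.

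**Inputs.**
- Population age shares 54/35/9/1% (section 2.8). They sum to 99% and are rescaled to 0.5455, 0.3535, 0.0909 and 0.0101.
- n = 1000 (section 2.8), N = 11,540 (section 2.4), level .05 (section 2.12), taken as two-sided.
- Assumed, because the documents do not give them: a population that is half men, and three sample mixes.

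**Formulas.** With population share P and sample share s in each of the eight age-by-gender cells, the mean-1 weight is w = P/s. The weighting design effect is deff = Σ s·w² = Σ P²/s. Age and gender are taken as independent here, so deff is the product of an age factor and a gender factor. If weights are read as counts, the true size of a nominal 5% test is 2·[1 − Φ(1.96/√deff)].

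**Moderate mix in full** (ages 35/43/19/3%, 60% men):
- Age factor: 0.5455²/0.35 + 0.3535²/0.43 + 0.0909²/0.19 + 0.0101²/0.03 = 0.850 + 0.291 + 0.043 + 0.003 = 1.188 (from unrounded terms).
- Gender factor: 0.5²/0.6 + 0.5²/0.4 = 1.042.
- deff = 1.188 × 1.042 = 1.24. Size = 2·[1 − Φ(1.96/1.112)] = 7.8%.

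**All three mixes, weights scaled to mean 1.** The simulated columns come from 4000 runs with n = 1000, eight cells and no true association.

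| Sample mix (assumed) | deff | Size, formula | Size, simulated chi-squared | Size, linearised variance | Size, unweighted |
|---|---|---|---|---|---|
| Mild: 45/40/13/2%, 55% men | 1.05 | 5.6% | 5.3% | 4.5% | 4.9% |
| Moderate: 35/43/19/3%, 60% men | 1.24 | 7.8% | 8.3% | 5.6% | 5.4% |
| Strong: 20/45/31/4%, 70% men | 2.14 | 18.0% | 18.1% | 5.2% | 4.9% |

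Logistic regression with weights as counts gave 5.3%, 8.3% and 18.0%. The simulation standard error at 5% is √(0.05 × 0.95/4000) = 0.34 percentage points, so the linearised and unweighted results are compatible with 5%.

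**Weights summing to 11,540.** The mean weight is then 11,540/1000 = 11.54, and the chi-squared statistic is multiplied by that factor. With no weight spread at all, the size is 2·[1 − Φ(1.96/√11.54)] = 56%. Multiplying each deff above by 11.54 gives 57%, 60% and 69% (simulated 57%, 60% and 70%).

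**Scale.** If all 21 items were null and each were a one-degree-of-freedom test, the expected false positives would be 21 × 0.05 = 1.1 at the nominal level, 21 × 0.078 = 1.6 in the moderate case and 21 × 0.18 = 3.8 in the strong case. This is only illustrative: some items have several categories, and some apply to one gender.

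**Limit of the check.** The simulation makes exposure and outcome unrelated to age and gender. It isolates the variance error and says nothing about confounding by age.

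**The case against.** The strongest reply is that section 2.12 never says the weights will be case counts. SPSS also has a Complex Samples module, so naming SPSS does not rule out a correct analysis. The article is a condensed protocol, and variance estimators and weight scaling are often left to an analysis plan. This stands against any unconditional claim. It does not dispose of the point, because the article is not silent on method: it names the test and the software and says that the same tests are run again with weights. Nothing in the text points to a survey procedure.

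Other parts of the reply also stand:
- With mild imbalance and mean-1 weights the error is negligible, and section 2.4 plans outreach to women's organisations, which works against a gender imbalance.
- The unweighted tests come first and do not have this fault.
- The primary outcome is a prevalence, and no hypothesis test is stated for it.
- A joint age-by-gender weight is already planned.

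A reader might go further and infer that the weighted P values and confidence intervals will certainly be wrong, that the software will act as if 11,540 people had been tested, or that the weighted results will displace the unweighted ones. The documents support none of these. They fix neither procedure nor scaling, mention no weighted intervals, and do not rank the two sets of results.

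**Conclusion.** The point holds conditionally. As written, the plan repeats ordinary tests with post-stratification weights and names no method that accounts for them. If the weights enter as case counts, the weighted P values for the secondary risk-factor analyses are too small.

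The size of the error depends on two things that the documents leave open. With mean-1 weights the true level runs from about 5.6% to 18% across the assumed mixes. With weights summing to the population it exceeds 50%, but nothing in the text says that this scaling is intended, so it marks the outer limit and is not an expectation. The range rests on the assumed mixes, an even gender split in the population and the Kish approximation, which the simulation supports under a simple null.

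The primary prevalence estimate is outside this point. The matter is worth correcting because the remedy is known, restores the level to about 5% in the simulation, and costs almost nothing.

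**What to change.** Add to section 2.12 that:

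1. all weighted analyses use survey procedures, for example SPSS Complex Samples or an equivalent package;
2. weighted contingency tables are tested with the Rao-Scott adjusted chi-squared test;
3. weighted logistic regression uses linearised or robust standard errors;
4. the joint age-by-gender weight, already among those planned, is the one used, normalised so that the weights sum to the number of persons tested.

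The cost is a sentence or two and a different software procedure. No additional data or participants are needed. Weighted standard errors and P values will be somewhat larger than those from weights treated as counts, and more so the more unequal the weights are.
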